## Trial management

A Trial Management Group (TMG) will provide overall supervision and ensure good conduct of the trial (i.e. adherence to the Declaration of Helsinki). The TMG will meet every three months during the course of this trial. In accordance with the MRC code of good practice in clinical trials and the CONSORT guidelines, we will document all decisions regarding eligibility for entry, consent giving, inclusion, exclusion and attrition. Members of the TMG will be: the researcher (NH) and members of the research team (VP, LS, PR, [name]). Every six months during data collection, the TMG will include an invited independent patients' advocate from the clinical stroke service.

## Discussion

This protocol describes an original, two-stage early phase trial, in which a group of early stroke survivors will first be evaluated for their ability to pedal a modified upright exercise cycle. Those who can pedal the cycle will then be participants in an early phase randomised controlled trial of daily pedalling intervention, for up to ten subsequent working days of their in-patient hospital stay.

Findings from neuroimaging studies suggest that rehabilitation programs incorporate repetition, motor skill acquisition and functional activity in order to optimally drive useful cortical plasticity [e.g. [10-14]]. It has been suggested that early rehabilitation intervention might exploit a crucial period in which the brain is primed to begin repair, in the first few days after stroke onset [1,2]. Therapists are therefore challenged to find rehabilitation strategies incorporating these underlying principles. Cycling provides a paradigm through which such activity might be achieved even in early stroke participants with severe weakness. For this trial, a prototype upright exercise cycle has been developed to enable such patients to experience bilateral pedalling motion. The locomotor strategies employed during cycling are akin to those used in ambulation [18] and our exercise cycle also incorporates adaptations to allow stroke survivors with considerable weakness to attempt to pedal in an upright posture, similar to walking.

Whilst evidence exists correlating clinical aspects of stroke to functional outcomes [e.g. [28-30]], prognostic information on what factors might influence the ability to take part in specific rehabilitation activities has yet to be established. This information has the potential to inform the design of future research and provide indicators to clinicians about which patients might best take part in which activities. The current trial will record four potential prognostic indicators-site of lesion, trunk control, paretic leg motor function and walking ability-before participants attempt to use the equipment; links to the ability to pedal the pedalling activity will be analysed and contribute to clinical conclusions and inform future research. For this novel aspect of the study, selection of potential indicators was based on those factors previously demonstrated to correlate to functional outcomes after stroke.

Some exploratory studies have investigated the potential clinical efficacy of pedalling exercise after stroke [20,24,25] but the early findings of our systematic review (in progress) suggest that no trial has evaluated upright pedalling in a group of stroke survivors within one month of stroke onset. The potential challenges that early stroke survivors might face in taking part in this activity, such as safely sitting in an upright posture and taking part in repetitive exercise, have been addressed: firstly by using a modified exercise cycle, and secondly, by ensuring that physiological parameters and evidence of fatigue are monitored and recorded by the research team.

It is possible that our results might indicate none of the prognostic indicators are linked to the ability to pedal, and/or clinical efficacy of the intervention is not demonstrated. If this is the case, the risk of wasting valuable research resources on larger-scale trials, using the current indicators and measures, is minimised. However, interpretation of findings, whether negative or positive, will reflect the small sample size and early phase nature of this work.

A further novel aspect is that this study of pedalling exercise incorporates biological level measures, alongside more frequently used clinical, functional measures. EMG data from quadriceps and hamstrings will be recorded at baseline and outcome as well as at each pedalling session, providing evidence of any change at a biological level that might contribute to, and underpin, possible changes in functional measures. Using sessional EMG recordings will also allow analysis of whether pedalling is being achieved by the unaffected leg propelling the crank i.e with the use of compensatory strategies, or whether there are changes in recordable activity in the affected leg suggestive of recovery.

The control group will undergo conventional therapy only, and this will be quantified on a standardised treatment schedule, allowing for comparisons of amount and type of therapy across trial arms. Concern has been expressed that reporting of research into complex interventions often lacks sufficient detail on comparators [42]. The use of careful recording of conventional therapy in this trial will go some way towards addressing these concerns and might provide important information for potential dose-matching in later phase work.

This trial is being carried out in an acute stroke unit, and uses portable EMG equipment so that all trial measures can be taken on site. This enables participants to take part in an active rehabilitation setting and hence exploration of the feasibility of the use of the modified bicycle in a busy therapeutic environment; and ensures close collaboration between clinical and research teams for the duration of data collection.

In summary, the proposed novel, early phase research will increase knowledge of prognostic indicators for, and clinical efficacy of, upright pedalling exercise early after stroke. It will provide essential information for the design of subsequent trials.

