**Methods/Design:**

Participants (n = 24) will be up to 30 days since stroke onset, with unilateral weakness and unable to walk without assistance. This study will use a modified exercise bicycle fitted with a UniCam crank. All participants will give informed consent, then undergo baseline measurements, and then attempt to pedal. Those able to pedal will be entered into a single-centre, observer-blinded randomised controlled trial (RCT). All participants will receive routine rehabilitation. The experimental group will, in addition, pedal daily for up to ten minutes, for up to ten working days.

Prognostic indicators, measured at baseline, will be: site of stroke lesion, trunk control, ability to ambulate, and severity of lower limb paresis.

The primary outcome for the RCT is ability to voluntarily contract paretic lower limb muscle, measured by the Motricity Index. Secondary outcomes include ability to ambulate and timing of onset and offset of activity in antagonist muscle groups during pedalling, measured by EMG.

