### Sample Size

This early phase trial is the first to use this equipment and with this participant group. Consequently there are no data to inform a power calculation. Sample size will therefore be based on practical considerations, using estimates of the number of participants we could expect to recruit within a 12 month time period. Using data from our previous trials of rehabilitation earIy after stroke [e.g [33]], we estimate a recruitment rate of two participants per month. Therefore, the sample size has been set at 24 participants.

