## Statistical Analysis

The aim of the analysis is not to definitively demonstrate efficacy in this early phase trial. Rather the data will be used to inform a decision on whether or not to undertake subsequent studies of UP. Assuming a normal distribution, independent t-tests will be used to compare groups between trial arms for follow-up measures, together with 95% confidence intervals to inform preliminary conclusions on clinical benefit. Within-group analysis will be assessed using paired t-tests. If a normal distribution cannot be assumed, analogous non-parametric methods will be used.

Associations between potential prognostic indicators and the ability to pedal will be examined using Fishers Exact test.

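### A null Fisher's exact test in 24 people cannot show that an indicator is unlinked to pedalling, yet the Discussion treats a null Aim 2 result as protection against wasted larger trials

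*Protocol article*

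**What the plan says.** Aim 2 is to determine whether lesion site, trunk control, severity of leg paresis or ambulatory ability predicts being able to use upright pedalling within 30 days of stroke. The Statistical Analysis section gives it one sentence: "Associations between potential prognostic indicators and the ability to pedal will be examined using Fishers Exact test". In the same section the comparison between arms is to be reported "together with 95% confidence intervals to inform preliminary conclusions on clinical benefit". No interval is mentioned for Aim 2.

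The Discussion considers what a null outcome would mean: "It is possible that our results might indicate none of the prognostic indicators are linked to the ability to pedal", and/or clinical efficacy might not be shown. It continues that in this event "the risk of wasting valuable research resources on larger-scale trials, using the current indicators and measures, is minimised". The next sentence says that findings in either direction will be interpreted with the small sample and early phase in mind.

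The Sample Size section explains that no data exist for a power calculation and that the number rests on feasibility: "Therefore, the sample size has been set at 24 participants". The Abstract applies that number to everyone who attempts to pedal: "Participants (n = 24) will be up to 30 days since stroke onset". Only those able to pedal are then randomised.

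**The concern.** A finding that an indicator is not linked to pedalling is a claim about absence. The one analysis named for Aim 2 tests for presence and, taken alone, returns a p-value. A large p-value in 24 people is to be expected both when an indicator is useless and when it is a fairly strong predictor. The Discussion nevertheless attaches a planning benefit to the null result.

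Aim 2 is one of the study's two aims, and the article says its results will inform the design of later research. If the Discussion's reading is carried forward, trunk control, leg paresis, walking ability or lesion site could be left out of later trials although the data remain compatible with a strong link. The saving of resources would then rest on a result that does not separate the two cases.

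**Working it through.** **Inputs from the protocol article.** The total is 24 (Sample Size; Abstract). It comes from "we estimate a recruitment rate of two participants per month" and the number of "participants we could expect to recruit within a 12 month time period": 2 × 12 = 24, which reproduces. There is no power statement to reproduce. There are four indicators, and the Aim 2 analysis is Fisher's exact test.

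**Assumptions not in the article.** Each indicator is reduced to two levels of 12 people each, the test is two-sided at 0.05, and pedalling rates are as listed below.

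**Step 1: how often one true predictor is missed.** Let X ~ Bin(12, p1) and Y ~ Bin(12, p2) be the numbers able to pedal at the two levels. Power is the sum of P(X = x)P(Y = y) over all tables with Fisher p ≤ 0.05, by full enumeration. The odds ratio is [p1/(1 − p1)] / [p2/(1 − p2)].

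| Able to pedal | Odds ratio | Power | Miss rate |
|---|---|---|---|
| 70% v 50% | 2.3 | 0.094 | 91% |
| 80% v 50% | 4.0 | 0.210 | 79% |
| 90% v 60% | 6.0 | 0.233 | 77% |
| 80% v 40% | 6.0 | 0.392 | 61% |
| 90% v 50% | 9.0 | 0.425 | 58% |
| 90% v 40% | 13.5 | 0.639 | 36% |
| 90% v 30% | 21.0 | 0.826 | 17% |

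With the better group's rate between 80% and 95%, power reaches 50% at an odds ratio of about 8 to 17, and 80% at about 16 to 30. The split matters. At 90% v 60%, power is 0.072 if only 6 of the 24 are in the better level and 0.318 if 16 are.

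**Step 2: when significance is out of reach.** With a 12/12 split and k people unable to pedal, the most extreme table puts all k at one level. Its two-sided p is 2 × C(12,k)/C(24,k):

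- k = 2: 2 × 66/276 = 0.478
- k = 3: 2 × 220/2024 = 0.217
- k = 4: 2 × 495/10626 = 0.093
- k = 5: 2 × 792/42504 = 0.037

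So with four or fewer unable, even perfect separation is non-significant. Few non-pedallers is plausible here. The cycle is adapted for severe weakness, the criterion is one minute of observed pedalling, and those who fail within 30 days of onset are offered reassessment about every three days.

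**Step 3: what an interval would show.** Suppose 9/12 v 7/12 are able. Fisher p = 0.67, and the exact conditional odds ratio is 2.07 with a 95% interval of 0.28 to 18.3. The p-value alone reads as no link. The interval shows that anything from a reversed association to a very strong one remains possible.

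**Step 4: the joint event the Discussion describes.** It speaks of none of the four being linked. If all four truly predicted, and if the tests were independent, the chance that all four are missed is (miss rate)^4:

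- 80% v 50%: 0.790^4 = 0.39
- 90% v 60%: 0.767^4 = 0.35
- 90% v 50%: 0.575^4 = 0.11

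These are well below the single-indicator rates. Positive correlation among the indicators would be expected to raise them, by an amount that cannot be derived from the article.

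**The case against.** The strongest reply is that the Discussion passage is not a rule. It is phrased as a possibility, joins the indicators to efficacy by and/or, sets no threshold, and is followed at once by a caveat about sample size. The article also says openly that 24 is a feasibility number. This stands. A reader might infer that any indicator with p above 0.05 will be dropped, but nothing in the article says so.

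A second reply is that this is a condensed article, and that an odds ratio with an interval for Aim 2 may be in a fuller analysis plan. Naming a test does not mean that only p-values will be reported. This also stands, so the absence of an interval is not in itself the point. The point is the inference that the article does state, which a fuller plan would not remove from the published text.

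A third reply is that the miss rates concern one indicator, whereas the text concerns all four. A reader might infer that true predictors would usually all be dismissed together. The calculation does not support that: at odds ratios of 4 to 9 the joint miss is about 11% to 39% under independence. Missing more often than not describes a single indicator, and only up to odds ratios of roughly 8 to 17.

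What remains is that the caveat asks for small-sample caution but names no quantity with which to exercise it.

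**Conclusion.** The concern holds in a limited form. The Discussion draws a planning benefit from a null Aim 2 result, and 24 people examined with Fisher's exact test cannot support it. Under a 12/12 split and a two-sided 5% level, a single true predictor is missed in 79% of studies at 80% v 50% able (odds ratio 4) and in 58% at 90% v 50% (odds ratio 9). With that split and four or fewer people unable to pedal, no significant result is possible. A null result therefore cannot show that an indicator is unlinked.

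The figures depend on the assumed split, level and pedalling rates, none of which the article gives, and on 24 being the number who attempt to pedal, as the Abstract has it. If 24 were instead the number randomised, Aim 2 would include more people and power would be somewhat higher.

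This is a weakness of inference and reporting in an exploratory aim. It does not affect the conduct of the trial or the comparison between arms.

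**What to change.** In Statistical Analysis, report for each indicator an estimate of association with an exact 95% confidence interval, alongside or in place of the Fisher p-value. Suitable measures are the area under the ROC curve for the ordered Motricity Index and Trunk Control Test scores, and the odds ratio for the Functional Ambulation Categories and lesion site.

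In the Discussion, state that a non-significant result at this sample size does not exclude a useful prognostic link and is inconclusive. Remove the claim that a null Aim 2 result minimises wasted resources.

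Do not add a formal cut-off for setting indicators aside. At this size it would be almost unusable: even an observed odds ratio of exactly 1 (6/12 v 6/12) has an exact 95% interval of 0.15 to 6.5.

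The cost is a few sentences and a few lines of analysis on data already planned, with no extra participants or procedures. The downside is that most null Aim 2 results will be reported as inconclusive, a less decisive message than the Discussion now offers.

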## Abbreviations

UP: UniCam crank-assisted upright pedalling; RCT: Randomised Controlled Trial; CPT: Conventional Physical Therapy; FAC: Functional Ambulatory Categories; MI: Motricity Index; TMG: Trial Management Group
